**Figure 2 F2:**
[figure not shown]
Study design of CARE-preserved HF. Patients will be randomized to either carvedilol-SR group or placebo groups. Carvedilol-SR, sustained-release carvedilol.

**Table 2 T2:** Standard protocol items: recommendation for interventional trials (SPIRIT) checklist.

	Study period			
	Enrolment (screening)	Allocation	Post-allocation	Close-out
Timepoint	Visit 1 (day −60–0)	Visit 2 (day 0)	Visit 2 (3 months)	Visit 3 (6 months)
Enrolment				
Eligibility screen	X			
Informed consent	X			
Allocation		X		
Interventions				
Intervention				
Control				
Assessments				
Baseline characteristics	X			
NT-proBNP	X	X		X
Echocardiography	X			X
12 lead electrocardiogram	X			
Vital signs	X	X	X	X
Secondary endpoints		X	X	X

NT-proBNP, N-terminal pro B-type natriuretic peptide.

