### Study outcomes and variables

The outcomes of this study are presented in Table 4. The primary efficacy outcome will be the time-averaged proportional change in NT-proBNP concentration from baseline through months 3 and 6. The secondary endpoints included the proportion of patients with an NT-proBNP decrease >20% from baseline through months 3 and 6, composite of all-cause mortality and all-cause hospitalization at 6 months. We will also assess changes in BP, HR, New York Heart Association (NYHA) classification, and quality of life at 6 months. Rate of BP control were under controlled will be compared between the two groups, which is defined as SBP <140 mmHg and diastolic BP <90 mmHg at 6 months. In addition, drug adherence and changes in echocardiographic parameters, including left atrial volume index, left ventricular mass index, E/e', e', pulmonary artery systolic pressure, and GLS will be assessed between the two groups. All adverse reactions and the incidence of the following adverse events of special interest during treatment will be assessed: symptomatic hypotension and bradycardia (investigator-reported).

**Table 4 T4:** Primary and secondary endpoints.

	Endpoints detail
Primary endpoint	Time-averaged proportional change in NT-proBNP concentration from baseline through months 3 and 6
Secondary endpoints	Proportion of patients with NT-proBNP decrease >20% from baseline through months 3 and 6
	Composite of all-cause mortality and all-cause hospitalization at 6 months
	Change in blood pressure and heart rate at 6 months
	Rate of blood pressure control at 6 months
	Change in NYHA classification at 6 months
	Change in quality of life assessed by visual analog scale (0–10)
	Drug adherence at 6 months
	Changes in echocardiographic parameter including LAVI, LVMI, E/e’, e’, pulmonary artery systolic pressure and GLS at 6 months

GLS, global longitudinal strain; LAVI, left atrial volume index; LVMI, left ventricular mass index; NT-proBNP, N-terminal pro B-type natriuretic peptide; NYHA, New York Heart Association.

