Blood sampling tests at the screening visit will be conducted by the laboratories at each participating institute, which are certified by the Korean Association of Quality Assurance for Clinical Laboratory. Measurement of NT-proBNP by an electro-chemiluminescence immunoassay method using cobas® 8,000 (Roche Diagnostics, Mannheim, Germany) will be performed in a central laboratory at randomization and at 6 months (visit 4). Quality of life will be assessed using a visual analog scale ranging from 0 to 10, with 0 being the worst and 10 being best. Drug adherence will be assessed by “pill count” measurements. The patients will bring the remaining tables to each scheduled visit, and trained and certified researchers will count the number of returned drugs and calculate drug adherence as follows:$$\text{Drug adherence }=\frac{\text{number of pills dispensed-number of pills returned}}{\text{number of days between dispensing date and follow-up date}}$$Baseline echocardiographic data collected within 2 months before randomization will be used. All images will be obtained using a standard ultrasound system with 2.5 MHz probes manufactured by GE, Phillips, and Siemens. Standard techniques will be used to obtain the M-mode, two-dimensional, and Doppler measurements. The LV dimensions, LVEF, and other echocardiographic parameters will be obtained according to the guidelines of American Society of Echocardiography and the European Association of Cardiovascular Imaging (32). Echocardiographic parameters at each institution will be archived in the Digital Imaging and Communications in Medicine format. GLS will be evaluated by a central echocardiography laboratory at the Samsung Medical Center, Seoul, Korea. GLS will be assessed using two-dimensional speckle-tracking echocardiography (2D-STE) on index echocardiography (33). The 2D-STE data will be analyzed using TomTec software (Image Arena 4.6, Munich, Germany) for deformation analyses (2-dimensional cardiac performance analysis) (27). For deformation analysis, endocardial borders are traced on the end-systolic frame in three apical views (4-, 2-, and 3-chamber), with end-systole defined by the QRS complex or as the smallest LV volume during the cardiac cycle. The software tracks speckles along the endocardial border and myocardium throughout the cardiac cycle. The peak longitudinal strain is computed automatically, generating regional data from six segments (anterior, anteroseptal, anterolateral, inferior, inferoseptal, and inferolateral) and an average value for each view. The GLS is determined as the average peak longitudinal strain of 18 LV segments from standard apical views. For patients with SR, analyses will be performed on a single cardiac cycle; for patients with AF, the strain values will be calculated as the average of three cardiac cycles. All strain measurements will be performed by strain specialists who are blinded to other data of each patient. All strain analyses will be performed by a single investigator. In our previous study, intra-observer variability in GLS was assessed in 30 randomly selected patients (34). The coefficient of variation has been identified as 5.8% for the GLS, and the intraclass correlation coefficient was 0.95 for GLS [95% confidence interval (CI), 0.91–0.98].

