
### Sample size and statistical analysis

To date, no previous study has evaluated the effects of carvedilol-SR on HFpEF. Due to the absence of prior research and the pioneering nature of our intervention, a sample size calculation was not conducted at this preliminary stage. As this was a pilot study to explore the benefit of carvedilol-SR for HFpEF, we decided to enroll a total of 100 participants (50 in the carvedilol-SR group and 50 in the control group) across the three institutes, considering the duration of the study and the number of participating hospitals.

Categorical variables will be reported as frequencies (percentages), and continuous variables will be expressed as means ± standard deviations or medians with interquartile ranges. Categorical variables will be compared using Pearson's chi-square test or Fisher's exact test, and continuous variables will be compared using Student's *t*-test or the Mann–Whitney *U*-test.

Primary analysis of the proportional change in NT-proBNP concentration from baseline on a logarithmic scale will be performed using an analysis of covariance model with an adjustment for the baseline value. This will be calculated as the average of the geometric means of NT-proBNP at months 3 and 6 divided by the geometric mean of NT-proBNP at baseline in a natural logarithmic scale (i.e., ratio of geometric means) and summarized as the difference between the treatment groups in the ratio of the geometric means. Cumulative clinical-event rates will be calculated according to the Kaplan–Meier method, and the differences in clinical outcomes between the two treatment groups will be assessed using the log-rank test. Hazard ratios and associated 95% CIs will be calculated using a Cox proportional-hazards model. The incidence of adverse events will be calculated as relative risks with associated 95% CIs.

Missing values due to unevaluable samples or early study discontinuation will not be imputed. Patients with missing baseline NT-proBNP and/or missing 3 and 6 months will not be included in the primary analysis. The data will be primarily analyzed using intention-to-treat analysis, including all randomized patients. We will also perform a per-protocol analysis, which include all randomized patients who receive at least one dose of the study drug during the double-blind period and have no major protocol deviations. Safety outcomes will be analyzed in the safety set of patients who received the trial drug at least once.

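### The primary endpoint averages NT-proBNP over months 3 and 6, but the article schedules no NT-proBNP measurement at month 3; the two must be reconciled

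*Protocol article*

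**What the plan says.** The endpoint side is consistent. Under Study outcomes and variables: "The primary efficacy outcome will be the time-averaged proportional change in NT-proBNP concentration from baseline through months 3 and 6". Table 4 and the Abstract give the same two follow-up months. Sample size and statistical analysis turns this into a formula: "the average of the geometric means of NT-proBNP at months 3 and 6 divided by the geometric mean of NT-proBNP at baseline", on the natural-log scale and with adjustment for baseline. The first secondary endpoint rests on the same visits: "Proportion of patients with NT-proBNP decrease >20% from baseline through months 3 and 6".

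The measurement side is also consistent, but it differs. Study outcomes and variables says that NT-proBNP measurement "will be performed in a central laboratory at randomization and at 6 months (visit 4" (closing bracket omitted here). Table 2 marks NT-proBNP at screening, allocation and 6 months, and leaves it empty in the column headed "Visit 2 (3 months" (closing bracket again omitted). Local testing is described for one visit only: "Blood sampling tests at the screening visit will be conducted by the laboratories at each participating institute".

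Intervention and follow-up places visits at 3 months (visit 3) and 6 months (visit 4). It lists laboratory tests among the contents of each visit and does not name NT-proBNP. The analysis section imputes nothing, and it drops from the primary analysis patients who lack baseline and/or the 3- and 6-month values.

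**The concern.** The defined outcome has three ingredients: baseline, month 3 and month 6. The schedule supplies two of them from the central laboratory. A site that followed the article would draw no NT-proBNP sample at 3 months, and the analyst would then have nothing to average with month 6.

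At stake is which primary endpoint the trial reports. If the gap is real and is found only at analysis, someone must choose between a month-6 endpoint and some other source for month 3, and no text guides that choice. A change of primary endpoint made at that stage is hard to defend, even in a pilot study. The first secondary endpoint inherits the same gap. If averaging is lost, some precision is lost with it.

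**Working it through.** **Step 1: passages side by side.**

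| Time point | Needed by the endpoint definition | Central assay in text | NT-proBNP row in Table 2 |
|---|---|---|---|
| Screening | no (eligibility only) | no (local laboratories) | marked |
| Randomization | yes (baseline) | yes | marked |
| 3 months | yes | not listed | blank |
| 6 months | yes | yes | marked |

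Only the 3-month row fails, and it fails in two separate places. A table-reading fault is an unlikely cause: the vital-signs row is marked in all four columns, so the 3-month column was read, and the prose omits the same visit.

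**Step 2: apply the missing-data rule to the schedule as written.** The rule can be read in two ways.
- If a patient is dropped when either follow-up value is missing, every patient lacks month 3 and 0 of 100 are evaluable.
- If a patient is dropped only when both are missing, everyone with a baseline and a month-6 value stays in, but the average consists of month 6 alone.

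Neither reading delivers the stated endpoint, and imputation is ruled out.

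**Step 3: illustrate the precision at stake.** The article gives no variance or correlation and no sample-size calculation, so there is no planned figure to reproduce. Assume that log NT-proBNP has unit variance at each visit, that the correlation rho is the same between any two visits, and that the treatment effect is equal at months 3 and 6. After adjustment for baseline:
- month 6 alone: variance = 1 − rho²
- mean of months 3 and 6: variance = (1 + rho)/2 − rho²

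| rho (assumed) | Month 6 only | Two-visit mean | Ratio | Square root of ratio |
|---|---|---|---|---|
| 0.5 | 0.75 | 0.50 | 1.50 | 1.22 |
| 0.6 | 0.64 | 0.44 | 1.45 | 1.21 |
| 0.7 | 0.51 | 0.36 | 1.42 | 1.19 |
| 0.8 | 0.36 | 0.26 | 1.38 | 1.18 |

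The square root is the relative width of the confidence interval, so at rho = 0.7 the interval is about 19% wider.

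**Step 4: put that loss in proportion.** At rho = 0.7, baseline adjustment cuts the variance from 1 to 0.51 (49%), and averaging then cuts it from 0.51 to 0.36 (0.15/0.51 = 29%). At 0.6 the cuts are 36% and 31%; at 0.8 they are 64% and 28%. Only at 0.5 does averaging contribute more (33% against 25%).

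**The case against.** The best defence is that this is a slip in a condensed article and that month-3 samples are being taken. The 3-month visit exists and includes laboratory tests. The missing-data rule speaks of 3- and 6-month values and of samples that cannot be evaluated, which reads as though month-3 sampling was planned. Table 2 is careless elsewhere: two columns carry the label visit 2, the 6-month column is called visit 3 although the text calls it visit 4, and the intervention and control rows are empty. Its generic row for secondary endpoints is marked at 3 months.

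This defence stands in part. A reader might infer that the trial has no month-3 data and that the endpoint cannot be delivered. The document does not show that; it shows only that its own statements conflict. The defence does not remove the conflict, however. The sentence on visit contents does not name NT-proBNP, and it is no dependable schedule, because it puts echocardiography at each visit while Table 2 marks it only at screening and 6 months. NT-proBNP has its own row in Table 2, blank at 3 months, so a generic row cannot fill it. Nor is this a detail left to the full protocol: the article states specific time points twice, and they disagree with its stated primary endpoint.

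Two further inferences go too far. One is that local month-3 results will be averaged with central ones. That is possible, but the text ties local laboratories to screening only. The other is that averaging two visits is the design's main source of precision. Step 4 shows that this fails for assumed correlations of 0.6 and above.

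**Conclusion.** The contradiction is certain and needs no assumption. The primary endpoint and the first secondary endpoint require a month-3 NT-proBNP value for which the article names no source. Taken literally, the schedule leaves either no evaluable patient or a month-6 endpoint under another name. Which side is wrong cannot be told from the document: if samples are taken at 3 months, the assay sentence and Table 2 are wrong; if not, the endpoint definitions are. Because it concerns the primary endpoint, it must be settled before unblinding.

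The size of the precision loss is an illustration only: a variance ratio of about 1.38 to 1.50 for rho from 0.8 to 0.5. It rests on an assumed rho, equal correlation between all visits and an equal effect at both visits. A month 3 to 6 correlation above the correlation with baseline would shrink the ratio. Dose is up-titrated at the physician's discretion, so the effect may differ between visits; if it were larger at month 6, a month-6 endpoint would lose less power than the ratio suggests. The ratio should not be turned into an equivalent number of patients per arm as if that were a shortfall, because the 100 patients were chosen without a power calculation.

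**What to change.** Establish first whether NT-proBNP is sampled at 3 months, and where it is assayed. Then:

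1. If it is or can be sampled, mark central-laboratory NT-proBNP at the 3-month visit in Table 2, and list randomization, 3 months (visit 3) and 6 months (visit 4) in the assay sentence.
2. Correct the Table 2 column labels to match the text: 3 months is visit 3 and 6 months is visit 4.
3. For patients already past month 3, use stored samples assayed centrally, if any exist. The article mentions none.
4. If central month-3 values were not and will not be collected, redefine the primary and first secondary endpoints before unblinding as month 6 versus baseline. Make the change in the Abstract, the outcomes text, Table 4, the analysis section and the registration, and report it as a change.

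The cost of the first route is one extra central assay per patient at a visit that already takes place, plus a formal amendment. It cannot recover everything: enrolment began in November 2021 and was expected to finish by early 2024, so month-3 values may be lost for some patients already enrolled. The fallback needs no new assay, but it amends the primary endpoint of a registered trial during its conduct and gives up the precision gained by averaging.

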
### Sample size and statistical analysis

To date, no previous study has evaluated the effects of carvedilol-SR on HFpEF. Due to the absence of prior research and the pioneering nature of our intervention, a sample size calculation was not conducted at this preliminary stage. As this was a pilot study to explore the benefit of carvedilol-SR for HFpEF, we decided to enroll a total of 100 participants (50 in the carvedilol-SR group and 50 in the control group) across the three institutes, considering the duration of the study and the number of participating hospitals.

Categorical variables will be reported as frequencies (percentages), and continuous variables will be expressed as means ± standard deviations or medians with interquartile ranges. Categorical variables will be compared using Pearson's chi-square test or Fisher's exact test, and continuous variables will be compared using Student's *t*-test or the Mann–Whitney *U*-test.

Primary analysis of the proportional change in NT-proBNP concentration from baseline on a logarithmic scale will be performed using an analysis of covariance model with an adjustment for the baseline value. This will be calculated as the average of the geometric means of NT-proBNP at months 3 and 6 divided by the geometric mean of NT-proBNP at baseline in a natural logarithmic scale (i.e., ratio of geometric means) and summarized as the difference between the treatment groups in the ratio of the geometric means. Cumulative clinical-event rates will be calculated according to the Kaplan–Meier method, and the differences in clinical outcomes between the two treatment groups will be assessed using the log-rank test. Hazard ratios and associated 95% CIs will be calculated using a Cox proportional-hazards model. The incidence of adverse events will be calculated as relative risks with associated 95% CIs.

Missing values due to unevaluable samples or early study discontinuation will not be imputed. Patients with missing baseline NT-proBNP and/or missing 3 and 6 months will not be included in the primary analysis. The data will be primarily analyzed using intention-to-treat analysis, including all randomized patients. We will also perform a per-protocol analysis, which include all randomized patients who receive at least one dose of the study drug during the double-blind period and have no major protocol deviations. Safety outcomes will be analyzed in the safety set of patients who received the trial drug at least once.

Primarily, we will assess the efficacy of carvedilol-SR on the reduction of NT-proBNP in HFpEF compared with a placebo. In addition, we will evaluate the differential effects of carvedilol-SR on primary outcomes according to prespecified variables, including baseline GLS, and NT-proBNP, LVEF. We planned to use the cutoff value of 14% GLS, taking into account a previous study (28), and also planned to use the median cutoff value of the GLS.

All tests will be two-tailed, and a *P*-value <0.05 will be considered statistically significant. Statistical analyses will be performed using R version 4.2.3 (The R Foundation for Statistical Computing, Vienna, Austria).

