1. ≥20 years of age, male or female 2. Patients with an SBP of ≥140 mmHg or a DBP of ≥90 mmHg, or if taking anti-hypertensive medication, an SBP of ≥110 mmHg. 3. Current symptom(s) of HF at screening visit^a^ 4. Elevated natriuretic peptides: NT-proBNP ≥220 pg/ml (BNP ≥80 pg/ml) for patients with SR or ≥660 pg/ml (BNP ≥240 pg/ml) for patients with AF at screening visit 5. LVEF ≥50% by echocardiography within 2 months before the randomization 6. Structural heart disease evidenced by one or both of the following echocardiography findings a) LAVI ≥29 ml/m^2^ in patients with SR or ≥34 ml/m^2^ in patients with AF b) LVMI ≥115 g/m^2^ in male or ≥95 g/m^2^ in female 7. Functional heart disease evidenced by at least one of the following echocardiography findings a) Average E/e’ ≥9 b) Septal e’ <7 cm/s c) Lateral e’ <10 cm/s d) Peak tricuspid regurgitation velocity >2.8 m/s e) Pulmonary artery systolic pressure >35 mmHg
Exclusion criteria

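### Change in NYHA class is an ordered secondary endpoint, but the plan's rule for categorical variables names only unordered tests; an ordered method that uses baseline class should be stated (minor)

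*Protocol article*

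**What the plan says.** Table 4 of the protocol article (Study outcomes and variables) lists "Change in NYHA classification at 6 months" among the secondary endpoints. It does not say whether this is a signed number of classes, an improved/same/worse grouping, or the class reached at 6 months.

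The section on sample size and statistical analysis has two general comparison rules in one sentence: "Categorical variables will be compared using Pearson's chi-square test or Fisher's exact test, and continuous variables will be compared using Student's" t-test or the Mann–Whitney test. The second rule in full is "continuous variables will be compared using Student's *t*-test or the Mann–Whitney *U*-test". The other methods named there are tied to other outcomes: analysis of covariance to NT-proBNP; Kaplan–Meier, log-rank and Cox to clinical events; relative risks to adverse events. No ordinal method is named. The significance rule is general: "All tests will be two-tailed, and a *P*-value <0.05 will be considered statistically significant".

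**The concern.** NYHA classes I to IV, and changes between them, have a natural order. Pearson's chi-square and Fisher's exact test on a table with more than two outcome categories do not use it: relabel the columns in any order and the P-value stays the same. Moving up a class and moving down a class are then just two different labels.

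Three things follow.

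- A consistent shift towards better classes is spread over several degrees of freedom and is easier to miss.
- The test has no direction and yields no effect estimate.
- It can be significant because one arm has both more improvers and more decliners.

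The endpoint has some weight here. The limitations section concedes that there is no objective functional measure such as a walk test or oxygen uptake, so NYHA class and the visual analog scale are the only endpoints on how patients feel and function.

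**Working it through.** **Which rule applies.** Once the outcome-specific methods are set aside, only the two general rules remain for NYHA change. A classification is categorical by name, and the rank test is offered for continuous variables only. The natural reading is therefore chi-square or Fisher. This is an inference, because the article does not make the assignment itself.

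**No planned figure to reproduce.** The article says that "a sample size calculation was not conducted at this preliminary stage", so no stated NYHA power exists.

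**Inputs from the article.** Arm sizes: "50 in the carvedilol-SR group and 50 in the control group". Two-sided 0.05. Entry requires "Current symptom(s) of HF at screening visit", so baseline class is taken as II or worse.

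**Inputs assumed, because the article gives none.**

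- Baseline class II/III/IV: 70/25/5%.
- Placebo cumulative probabilities at 6 months of class I, ≤II and ≤III: 0.30/0.90/0.99 from baseline II, 0.10/0.50/0.95 from III, 0.03/0.25/0.70 from IV.
- A common odds ratio (OR) multiplies the cumulative odds in the active arm. Example: from class II the placebo odds of class I are 0.30/0.70 = 0.429; with OR 2.5 they become 1.071, a probability of 1.071/2.071 = 0.52.
- No dropout.

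**Simulated power (%), 50 per arm.** Simulation error is about one point.

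| Coding and test | OR 2.0 | OR 2.5 | OR 3.0 |
|---|---|---|---|
| Full change, chi-square | 22 | 38 | 54 |
| Full change, Mann–Whitney | 40 | 60 | 76 |
| Full change, rank test stratified by baseline class | 42 | 63 | 78 |
| Improved/same/worse, chi-square | 30 | 49 | 66 |
| Improved/same/worse, Mann–Whitney | 38 | 60 | 76 |
| Improved or not, chi-square | 38 | 59 | 76 |

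Mann–Whitney minus chi-square on the full change: 40 − 22 = 18, 60 − 38 = 22 and 76 − 54 = 22 points. With baseline mixes of 60/35/5% and 85/15/0% added, the range is 17 to 22. On improved/same/worse the gaps are 8, 11 and 10. Chi-square on the dichotomy is within 0 to 2 points of Mann–Whitney on the full change.

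**Check that needs no NYHA distribution.** Suppose the effect is a shift that a 1-df ordered test detects with power P. The noncentrality is λ = (z(0.975) + z(P))². For P = 80%, λ = (1.960 + 0.842)² = 7.85. The power of an unordered test on k df is the probability that a noncentral chi-square(k, λ) exceeds its 5% critical value.

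| 1-df power | 2 df | 3 df | 4 df |
|---|---|---|---|
| 80% | 70.9% | 64.5% | 59.5% |
| 50% | 40.1% | 34.5% | 30.8% |

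Over a grid of P from 30% to 90%, the largest loss is about 10.5 points on 2 df, 17 on 3 df and 22 on 4 df. The number of occupied categories therefore drives the loss. In the simulated model the full change table averages about 3.6 df. It is also sparse: Pearson's test has type I error 0.033 against 0.044 for Mann–Whitney, so part of the 18 to 22 points comes from a conservative test rather than from lost ordering.

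**Other distributions, proportional odds, OR 1.5 to 4.** The gap is 0 points with two categories, about 3 to 11 with three, 7 to 19 with four and 9 to 24 with five.

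**Non-uniform effects (improved/same/worse).**

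- 20/70/10 versus 40/50/10: chi-square 51.3%, Mann–Whitney 43.6%, a reversal of about 8 points.
- 25/65/10 versus 45/40/15, where both improvement and worsening rise: chi-square 61.4%, Mann–Whitney 28.1%, a reversal of about 33 points. Here the unordered test responds largely to a difference in spread.

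**The case against.** The strongest reply is that nothing in the article sends NYHA change to chi-square. The outcomes section names it alongside changes in blood pressure, heart rate and quality of life, all numeric, and the sentence with the categorical rule goes on to name the Mann–Whitney test. If the change is scored as a number of classes, the plan already contains a suitable rank test, and stratifying it by baseline class adds only 2 to 3 points in the table above. Matching each secondary endpoint to a coding and a test is also commonly left to a full protocol or SAP, which is not shown.

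Part of this stands. The assignment is an inference, and the missing coding alone would not be a finding. But the article does not simply stay silent: it lays down a rule for categorical variables generally and limits the rank test to continuous ones. That rule is unsuitable for an ordered endpoint. If Mann–Whitney is intended, the text should say so, because as written an analyst could defend either test and the two can disagree.

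A reader might infer that the plan loses 20 points of power on this endpoint. The documents do not support that: they give no distribution, coding or effect, and the figure moves from 0 to 24 points, or below zero, with those choices. A reader might also infer that a significant result would leave the better arm unknown. That goes too far: categorical variables are to be reported as frequencies and percentages, so the direction can be seen in the table even though the test does not assess it.

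**Conclusion.** The point holds as a minor one. On the natural reading, an ordered secondary endpoint gets an unordered test. Against a consistent shift at 50 per arm and odds ratios of 2 to 3, the cost is about 18 to 22 points of power on the full change categories, about 10 on improved/same/worse and near zero on a dichotomy. These figures rest on an assumed baseline mix, assumed placebo transitions, proportional odds and no dropout. The ordered test is not better against every alternative. The case for it is that it addresses whether patients on one arm end up in better classes, and gives that answer a direction.

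The severity is low because this is one of several secondary endpoints in a pilot with no power calculation, and the NT-proBNP analysis does not depend on it.

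**What to change.** In the section on sample size and statistical analysis, state that NYHA class at 6 months will be compared with an ordered method that uses baseline class. Either of these would do:

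- a proportional-odds model for 6-month class with treatment and baseline class, reported as a common odds ratio with 95% CI; or
- a Wilcoxon–Mann–Whitney test on the change in class, stratified by baseline class.

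State how the change is coded, and limit Pearson's chi-square and Fisher's exact test to binary or nominal variables.

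The cost is one sentence before unblinding, with no new data or patients. The small downside of the model is the proportional-odds assumption, which the stratified rank test largely avoids.
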